## Abstract

**Background:**

Patients with metastatic colorectal cancer whose disease has progressed on oxaliplatin- and irinotecan-containing regimens may benefit from EGFR-inhibiting monoclonal antibodies if they do not contain mutations in the *KRAS* gene (are “wild type”). It is unknown whether these antibodies, such as cetuximab, are more efficacious in refractory metastatic colorectal cancer as monotherapy, or in combination with irinotecan. Lack of mutation in *KRAS*, *BRAF* and *PIK3CA* predicts response to EFGR-inhibitors. The ICECREAM trial examines the question of monotherapy versus combination with chemotherapy in two groups of patients: those with a “quadruple wild type” tumour genotype (no mutations in *KRAS, NRAS, PI3KCA* or *BRAF* genes) and those with the specific *KRAS* mutation in codon G13D, for whom possibly EGFR-inhibitor efficacy may be equivalent.

**Methods and design:**

ICECREAM is a randomised, phase II, open-label, controlled trial comparing the efficacy of cetuximab alone or with irinotecan in patients with “quadruple wild type” or G13D-mutated metastatic colorectal cancer, whose disease has progressed on, or who are intolerant of oxaliplatin- and fluoropyrimidine-based chemotherapy. The primary endpoint is the 6-month progression-free survival benefit of the treatment regimen. Secondary endpoints are response rate, overall survival, and quality of life. The tertiary endpoint is prediction of outcome with further biological markers. International collaboration has facilitated recruitment in this prospective trial of treatment in these infrequently found molecular subsets of colorectal cancer.

**Discussion:**

This unique trial will yield prospective information on the efficacy of cetuximab and whether this is further enhanced with chemotherapy in two distinct populations of patients with metastatic colorectal cancer: the “quadruple wild type”, which may ‘superselect’ for tumours sensitive to EGFR-inhibition, and the rare *KRAS* G13D mutated tumours, which are also postulated to be sensitive to the drug. The focus on establishing both positive and negative predictive factors for the response to targeted therapy is an attempt to improve outcomes, reduce toxicity and contain treatment costs. Tissue and blood will yield a resource for molecular studies. Recruitment, particularly of patients with the rare G13D mutation, will demonstrate the ability for international collaboration to run prospective trials in small colorectal cancer molecular subgroups.

**Trial registration:**

Australian and New Zealand Clinical Trials Registry: ACTRN12612000901808, registered 16 August 2012.

## Background

The ICECREAM study (Irinotecan Cetuximab Evaluation and the Cetuximab Response Evaluation Among Patients with G13D Mutation) aims to provide prospective data on the optimal use of targeted therapies in patients with metastatic colorectal cancer (mCRC) whose tumours have progressed on standard chemotherapy. The trial will study two preselected patient populations in parallel, to determine whether cetuximab is optimally used as monotherapy, or in combination with an irinotecan-based regimen. In retrospective studies, the “quadruple wild type (WT) ” genotype (no mutations in *KRAS, NRAS, PI3KCA* or *BRAF* genes) appears to select responders to EFGR-inhibitors (EGFR-I) over and above that of *KRAS* exon 2 WT alone, which was until recently the extent of standard mutation testing. Similarly, retrospective data suggest that patients whose tumours harbour the specific *KRAS* G13D mutation may be sensitive to EGFR-I, in contrast to all other *KRAS* mutations. To date, no prospective trials of EGFR-I selected by tumour mutation/WT status have been undertaken.

Trial results may affect the standard of treatment for both groups of patients, in particular defining both a highly sensitive group and potentially providing the foundation for access to EGFR-I treatment for patients with *KRAS* G13D mutated mCRC. The trial was devised and instigated as an investigator initiated study in Australia, with participation of leading cancer institutes in Italy, Spain, Belgium and England.

### Rationale for evaluating the addition of irinotecan to cetuximab in WT patients

The BOND study, undertaken in patients with irinotecan-refractory mCRC demonstrated a modest progression-free survival (PFS) benefit for cetuximab in combination with irinotecan compared with cetuximab alone [1]. Whilst the benefits were modest, toxicity was increased with the combination. Also, due to being conducted in an era prior to RAS testing, as well as the lack of tissue availability, RAS testing has not been retrospectively performed on the BOND cohort. Therefore it remains unclear whether the addition of irinotecan will provide additive benefit in patients selected for *KRAS* WT tumours. The landmark EGFR-I phase III trials in refractory mCRC elected to use the EGFR monoclonal antibodies (cetuximab and panitumumab) as monotherapy [2–4]; however, clinical use in Australia and worldwide is divided equally between monotherapy and doublet therapy in the refractory setting. Therefore, the use of cetuximab alone versus combination with irinotecan remains an important, unanswered question.

### Rationale for studying “quadruple wild type” tumours

EGFR-I administration is now restricted to patients with *RAS* WT tumours, following retrospective analyses that initially demonstrated lack of mutation in *KRAS* exon 2 (codons 12 and 13) as a positive predictive marker [4, 5], with subsequent extension of predictive molecular markers to include other exons of *KRAS* as well as of *NRAS* (exons 2, 3, 4) [6–8]. Less certain, but suggestive are data showing that sensitivity to EGFR-I also depends on the WT status of *BRAF* (exon 15) and *PIK3CA* (exon 20) genes [9, 10].

### Rationale for studying EGFR-I in patients with G13D mutations

Multiple retrospective analyses, initially in refractory mCRC [11], then in 1^st^ and 2^nd^ line chemotherapy-EGFR-I combinations [12], suggested that the subgroup with the specific codon 13 mutation: G13D appear to derive benefit from cetuximab therapy to a similar extent as *KRAS* WT patients. This is also supported in a meta-analysis [13]. The KRAS exon 2 mutation c.38G > A: pGly13Asp (G13D) accounts for ~19 % of KRAS mutations, with an absolute incidence of 8 % in mCRC [11]. Preclinical studies in cell lines and xenograft models have demonstrated a response to cetuximab and blockade of the EGFR kinase pathway in the G13D mutants, but not in other (eg G12V) mutants [11]. Based on this data, the use of cetuximab for these patients harbouring the rare G13D KRAS mutation is becoming an increasingly relevant clinical predicament.

Results from the treatment of patients with G13D mutations varied in a pooled analysis of trials with panitumumab (a fully humanized EGFR-I) covering all lines of treatment of mCRC [14]. In one first line study, patients with a G13D mutation treated with panitumumab had an unfavourable overall survival, whereas patients with a G12V mutation had a favourable outcome, which was the opposite finding to cetuximab studies [6]. However, analysis of outcomes of patients with G13D tumours showed a trend to benefit from panitumumab when compared with placebo [14]. These data further support the need for prospective studies in patients with G13D tumour mutations.

The enriched group of patients being examined in the ICECREAM trial will yield valuable information regarding other features associated with response to EGFR-I, in particular the depth of response to treatment, which has been shown to be a predictor of clinical benefit and survival [15–17]. Biological substudies examining additional biomarkers in both subgroups are planned.

## Methods and design

### Study design and objectives

ICECREAM is a randomised, open-label, phase II study of cetuximab monotherapy versus the combination of cetuximab and irinotecan. The primary objective is to determine the 6-month progression free survival (PFS) benefit of cetuximab alone or in combination with irinotecan in patients with *KRAS, NRAS, BRAF* and *PIK3CKA* wild type mCRC or *KRAS* G13D mutated mCRC. PFS is defined as the time from randomisation to disease progression according to RECIST criteria, version 1.1 [18]. Secondary objectives are to determine the response rate (as complete or partial responses according to RECIST criteria, version 1.1) in patients with “quadruple wild type” or *KRAS* G13D mutated mCRC. Overall survival benefit in the two patient cohorts will be determined based on death from any cause. The study will evaluate quality of life with FACT-C (Functional Assessment of Cancer Therapy), DLQI (Dermatology Quality of Life Index Questionnaire), and FACT-EGFRI 18 (Functional Assessment of Cancer Therapy, pertaining specifically to Epidermal Growth Factor Receptor Inhibition).

Tertiary and correlative objectives are to undertake exploratory studies of biological markers as predictors of outcome. Early tumour response will be measured by assessment of tumour shrinkage on CT imaging performed at 6 weeks post first treatment, based on independent review of volumetric tumour size.

Biological substudies aim to improve understanding of the mechanisms of cetuximab and any interaction with irinotecan in wild type and G13D mutated tumours. Since the identification of new biomarkers correlating with disease activity, and the efficacy and safety of treatments are rapidly evolving, a definitive list of biomarker studies remains to be determined at the time of these studies.

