### Statistical methods

The sample size of 100 patients is comprised of 50 patients with confirmed “quadruple wild type” status and 50 patients with a confirmed G13D tumour mutation. An intention to treat analysis will be undertaken, with the inclusion of all randomised patients.

In keeping with the randomized phase II study design, PFS was selected as the appropriate primary endpoint as this would not be influenced by subsequent cross over from monotherapy to combination treatment, which may occur at progression on study. Statistical assumptions were on the basis of retrospective data (Table 1) with a median PFS of 1.8 months in the cetuximab-alone arm versus 4.0 months for patients with KRAS G13D–mutated tumors receiving any cetuximab therapy [11]. This corresponds to a 6-month PFS rate of approximately 10 % for the monotherapy group and 35 % for the combination group. The G13D component of the study planned to recruit 25 patients per arm to match the wild-type cohort. This enabled 80 % power (α = .05) to detect an improvement from 15 to 40 % in 6-month PFS by using the Simon design for phase II trials. This magnitude of effect was chosen because we were interested in detecting a similar degree of benefit in the KRAS G13D–mutation population that was anticipated to be practice changing in patients with wild-type tumors. PFS and OS treatment effects were described by using hazard ratios (HRs) that were estimated by using Cox proportional hazards models. Completeness of the PFS was estimated by using a published equation [19]. Waterfall plots were constructed by using the biggest decrease compared with baseline in the sum of the target lesions. Patients with a decreased sum of target lesions but with new non-target lesions were set to a zero change but still qualified as having progressive disease. QoL changes over time were modeled by using generalized estimating equations. Analyses used SAS v9.3 (SAS Institute, Cary, NC).

**Table 1 Tab1:** Summary of current clinical trial PFS data on which statistical calculations are based

	KRAS unknown	KRAS WT	KRAS mutant	KRAS G13D
BOND study [1] cetuximab alone vs cetuximab + irinotecan	6 m PFS = 8 % vs. 30 %	NA	NA	NA
CO.17 [4] cetuximab vs best supportive care	N/A	6 m PFS cetuximab = 30 %	6 m PFS < 5 %	
De Roock [11] cetuximab vs no cetuximab	N/A	Median PFS 4.2 m vs 1.9 m	Median PFS 1.9 m vs 1.8 m	Median PFS 4.0 m vs 1.7 m

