### Planned futility analysis

As the activity of the combination is of particular interest in patients with G13D KRAS mutated tumours, Simon’s II stage design was applied to this group of patients. Futility will be declared if in the first seven eligible patients having at least six months of combination treatment, all seven patients have progressed.

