### Pre-trial screening procedures and randomisation and stratification

Entry into the study is conditional on confirmation of tumour genotype by means of mutation analysis of representative samples of diagnostic tumour tissue. *KRAS* G13D status is determined by local pathology laboratories, whereas “quadruple wild type” status is determined by a central reference laboratory, the Centre for Translational Pathology, Melbourne, Australia. Archival tumour samples from the primary colorectal cancer or any metastatic site are acceptable for mutation analysis. All specimens are received as formalin fixed, paraffin embedded tissue biopsy blocks (FFPE), which upon arrival are cut into 10 μm sections by microtome and transferred onto glass slides before de-waxing and DNA extraction. An additional 4 μm slide section is stained with haematoxylin and eosin, examined by a pathologist to determine and mark the region of tumour, and then used to determine the areas of tumour to be macrodissected from unstained slides. DNA is extracted using Qiagen FFPE DNA extraction kits and successful DNA extraction is confirmed by Qubit DNA quantitation and LabChipGX DNA fragmentation assessment. For Sanger sequencing, targeted regions of interest from exon 15 of the BRAF gene, exons 9 and 20 of the PIK3CA gene, and exons 2, 3, and 4 of both KRAS and NRAS genes are amplified separately by PCR and sequenced using BigDye terminator chemistry on an ABI 3730 genetic analyser. Mutation analysis uses Mutation Surveyor software. For next generation sequencing (NGS) analysis, targeted regions of interest from exon 15 of the BRAF gene, exons 9 and 20 of the PIK3CA gene, and exons 2, 3, and 4 of both KRAS and NRAS genes are amplified and linked to barcoded NGS adapters with a two-step multiplex PCR protocol. The resulting library is sequenced on an Illumina MiSeq next generation sequencer. Mutations are detected with MiSeq Reporter software.

Written informed consent must be obtained, and patients must be randomised before starting the study treatment and planned to start within 14 days of randomisation.

Patients are centrally randomised in a 1:1 ratio and be stratified according to “quadruple wild type” or *KRAS* G13D mutational status, and treating hospital. This publication represents the current protocol version (V4).

The ICECREAM trial opened in November 2012 with a recruitment period of two years.

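### The primary endpoint is called PFS but is defined by RECIST progression alone, so a death without documented progression is not counted as a failure

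*Protocol article*

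**What the plan says.** Study design and objectives gives the definition outright: "PFS is defined as the time from randomisation to disease progression according to RECIST criteria, version 1.1". Shortly afterwards the same section brings in death, but for a different endpoint: "Overall survival benefit in the two patient cohorts will be determined based on death from any cause". No other section adds death to PFS or says how a death without documented progression is classified.

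Planned futility analysis, which applies to the G13D cohort, uses the same event: "Futility will be declared if in the first seven eligible patients having at least six months of combination treatment, all seven patients have progressed".

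Statistical methods sets the target for that cohort, which "planned to recruit 25 patients per arm to match the wild-type cohort", as 80 % power at α = .05 "to detect an improvement from 15 to 40 % in 6-month PFS by using the Simon design for phase II trials". It also commits to an intention-to-treat analysis of everyone randomised, so every early death has to be classified somehow.

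**The concern.** An endpoint whose only event is RECIST progression is time to progression, whatever its label. In refractory metastatic disease a patient who dies before progression is documented has failed treatment. Under the printed definition that patient is not a failure. The text does not say what happens instead; the two natural options are censoring at death or counting the patient as not progressed. Either raises the estimated 6-month rate unless there are no such deaths.

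Such deaths are plausible. Inclusion criteria requires a life expectancy of at least 12 weeks, which is shorter than the 6-month horizon of the endpoint.

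Two decisions are exposed: whether an arm's 6-month rate looks better than 15 %, and whether the G13D combination arm stops early for futility.

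**Working it through.** **Inputs.** From Statistical methods: null 15 %, target 40 %, 25 per arm, 80 % power, α = .05. From Planned futility analysis: stop if 7 of 7 have progressed, that is, 0 of 7 progression-free. Assumed: f, the share of failures that are deaths without documented progression, set at 0, 5, 10 and 20 % because the document gives no figure.

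**Step 1: the plan's own figure.** An exact binomial search for Simon's optimal design (15 % against 40 %, one-sided α at most 0.05, power at least 0.80) gives 7 patients in stage 1 and 25 in total. It stops at ≤1 of 7 and rejects at ≥7 of 25, with α = 0.049 and power 0.806. So n = 25 and 80 % power are reproduced. The article, however, prints a stop at 0 of 7 and no final cut-off. With the printed stop, rejecting at ≥7/25 gives α = 0.066 and power 0.909; rejecting at ≥8/25 gives α = 0.025 and power 0.834.

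**Step 2: apparent 6-month rate when the true progression-or-death-free rate is p = 0.15.**
- Deaths censored, proportional cause-specific hazards: p^(1−f). For f = 10 %, 0.15^0.90 = 0.181.
- Deaths counted as not progressed: p + f(1−p). For f = 10 %, 0.15 + 0.10 × 0.85 = 0.235.

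**Step 3: false-positive rate (illustrative).** The censored rate q from step 2 goes into the binomial rule with the printed 0/7 stop:

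P(reject) = Σ over x = 1 to 7 of P[Bin(7, q) = x] × P[Bin(18, q) ≥ c − x], with c = 7 or 8.

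**Step 4: futility stop.** If the seven are patients followed for six months, P(stop) = (1 − q)^7, here with deaths counted as not progressed. For f = 0, 0.85^7 = 0.321; for f = 10 %, 0.765^7 = 0.153.

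| f | Rate, deaths censored | False positive, ≥7/25 | False positive, ≥8/25 | Rate, deaths as not progressed | P(stop at 0/7) |
|---|---|---|---|---|---|
| 0 % | 15.0 % | 6.6 % | 2.5 % | 15.0 % | 0.32 |
| 5 % | 16.5 % | 9.9 % | 4.1 % | 19.3 % | 0.22 |
| 10 % | 18.1 % | 14.5 % | 6.6 % | 23.5 % | 0.15 |
| 20 % | 21.9 % | 28.5 % | 15.8 % | 32.0 % | 0.07 |

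**Step 5: the other reading of the futility rule.** Taken literally, the seven must each have had at least six months of combination treatment. A patient who dies early is then not among the seven and cannot block the stop; the failure simply drops out of the count. That reading also sits badly with Administration of study treatment, where treatment ends at progression: a patient who progresses early would not reach six months of treatment either. The two sections must be reconciled.

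**Step 6: with death counted as an event.** The stop probability is 0.85^7 = 0.321 at a true 15 % and 0.60^7 = 0.028 at a true 40 %. The sample size does not change.

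**The case against.** The strongest reply is that this is a drafting slip. The endpoint is called progression-free survival throughout, the article condenses a longer protocol, and rules for deaths and censoring usually sit in an analysis plan that is not shown. The intended definition may well include death. But the article does not leave the event open: it states a complete definition, and says that it represents the current protocol version. If a fuller document counts deaths, the two conflict and this text still needs correcting.

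The second reply is that the size is unknown, and this stands. Every figure scales with f, and at f = 0 nothing changes. Some features point to a low share: ECOG 0–1, at least 12 weeks' life expectancy, and a CT at 6 weeks.

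The third concerns the false-positive figures. They put a censored-survival rate into a count rule that does not censor, and the final cut-off is not printed. They illustrate sensitivity and are not the trial's error rate. A reader might start from the textbook Simon design and quote a rise from 4.9 %, but that design stops at ≤1 of 7, which is not the printed rule.

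Three further inferences are tempting and not supported:
- That one early death always prevents a futility stop. This holds only if the seven are defined by follow-up and not by treatment received.
- That the observed rates would not be comparable with the Table 1 studies. The documents do not say how those studies defined PFS, and the 15 % bar is not itself a Table 1 figure.
- That the comparison of arms is biased in a known direction. The Cox hazard ratio could move either way, depending on how such deaths fall between the arms.

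**Conclusion.** The point holds as a defect in the stated definition of the primary endpoint. The omission of death is certain from the text. So is the direction of its effect on each arm's 6-month rate: upward or nil.

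The magnitude is conditional on f, for which the documents offer no value. With deaths censored under proportional hazards, a true 15 % reads as 16.5 % at f = 5 % and as 21.9 % at f = 20 %. The loss of futility stopping holds under the follow-up reading only, with deaths counted as not progressed. The false-positive rates rise under both cut-offs examined but remain illustrative.

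**What to change.** In Study design and objectives, define PFS as the time from randomisation to RECIST 1.1 progression or death from any cause, whichever comes first.

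In Planned futility analysis, identify the seven as eligible combination-arm patients followed for six months from randomisation, and count as a failure any patient who has progressed or died. This also removes the ambiguity over six months of treatment.

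The cost is two wording changes and a possibly lower observed PFS. Deaths are already needed for overall survival, so no new data are required, and n = 25 per arm stays as it is.

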### Trial organisation

The trial was developed by Australian clinicians in collaboration with key international clinicians. The Australasian Gastrointestinal Trials Group (AGITG) is the study sponsor and the trial is coordinated by the NHMRC Clinical Trials Centre (CTC) at the University of Sydney, Australia. The legal sponsor in the European Union (EU) is Hammersmith Hospital. Randomisation and data collection are performed electronically and the CTC is responsible for management of safety, ethical and regulatory reporting, central coordination of study sites and management of statistical analyses. The trial is registered on the Australian and New Zealand Clinical Trials Registry (ACTRN12612000901808).

### Statistical methods

The sample size of 100 patients is comprised of 50 patients with confirmed “quadruple wild type” status and 50 patients with a confirmed G13D tumour mutation. An intention to treat analysis will be undertaken, with the inclusion of all randomised patients.

In keeping with the randomized phase II study design, PFS was selected as the appropriate primary endpoint as this would not be influenced by subsequent cross over from monotherapy to combination treatment, which may occur at progression on study. Statistical assumptions were on the basis of retrospective data (Table 1) with a median PFS of 1.8 months in the cetuximab-alone arm versus 4.0 months for patients with KRAS G13D–mutated tumors receiving any cetuximab therapy [11]. This corresponds to a 6-month PFS rate of approximately 10 % for the monotherapy group and 35 % for the combination group. The G13D component of the study planned to recruit 25 patients per arm to match the wild-type cohort. This enabled 80 % power (α = .05) to detect an improvement from 15 to 40 % in 6-month PFS by using the Simon design for phase II trials. This magnitude of effect was chosen because we were interested in detecting a similar degree of benefit in the KRAS G13D–mutation population that was anticipated to be practice changing in patients with wild-type tumors. PFS and OS treatment effects were described by using hazard ratios (HRs) that were estimated by using Cox proportional hazards models. Completeness of the PFS was estimated by using a published equation [19]. Waterfall plots were constructed by using the biggest decrease compared with baseline in the sum of the target lesions. Patients with a decreased sum of target lesions but with new non-target lesions were set to a zero change but still qualified as having progressive disease. QoL changes over time were modeled by using generalized estimating equations. Analyses used SAS v9.3 (SAS Institute, Cary, NC).

**Table 1 Tab1:** Summary of current clinical trial PFS data on which statistical calculations are based

	KRAS unknown	KRAS WT	KRAS mutant	KRAS G13D
BOND study [1] cetuximab alone vs cetuximab + irinotecan	6 m PFS = 8 % vs. 30 %	NA	NA	NA
CO.17 [4] cetuximab vs best supportive care	N/A	6 m PFS cetuximab = 30 %	6 m PFS < 5 %	
De Roock [11] cetuximab vs no cetuximab	N/A	Median PFS 4.2 m vs 1.9 m	Median PFS 1.9 m vs 1.8 m	Median PFS 4.0 m vs 1.7 m
Tepjar [12] cetuximab vs no cetuximab as 1st line treatment	Not relevant	Median PFS 9.6 m vs 7.6 m	Median PFS 6.7 m vs 8.1 m	Median PFS 7.4 m vs 6.0 m

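### The planning medians are labelled monotherapy and combination, but Table 1 shows their source as cetuximab versus no cetuximab, and the stated 80% power belongs to a one-arm test that does not isolate irinotecan

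*Protocol article*

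**What the plan says.** The Statistical methods section of the protocol article bases its assumptions on a "median PFS of 1.8 months in the cetuximab-alone arm versus 4.0 months for patients with KRAS" G13D, where the second group is described as "mutated tumors receiving any cetuximab therapy [11" (reference 11). The next sentence turns the two medians into rates: "This corresponds to a 6-month PFS rate of approximately 10 % for the monotherapy group and 35 % for the combination group". The section then claims 80% power at α = 0.05 to detect a rise from 15% to 40% in six-month PFS with 25 patients per arm in the G13D component, using the Simon design.

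Table 1, in the same section, heads the row for reference 11 "cetuximab vs no cetuximab". Its cells are:

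- KRAS wild type: "Median PFS 4.2 m vs 1.9 m"
- KRAS mutant: "Median PFS 1.9 m vs 1.8 m"
- KRAS G13D: "Median PFS 4.0 m vs 1.7 m"

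Under Administration of study treatment, both Arm A and Arm B receive cetuximab; they differ only in irinotecan. Planned futility analysis applies Simon's two-stage design to the G13D group because the activity of the combination is of interest there, and stops if all of the first seven combination patients have progressed.

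**The concern.** The text and the table give the same figures different meanings. In the text, 1.8 and 4.0 months are cetuximab alone and the combination. In the table, the row that holds both numbers compares cetuximab with no cetuximab, and its only 1.8 belongs to KRAS-mutant patients without cetuximab. The no-cetuximab figure for G13D is 1.7. Read from the table, the assumed gain of 25 percentage points is the effect of giving cetuximab at all, which this trial does not vary.

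The interpretation of a positive result is at stake. A test of Arm B against a fixed 15% can succeed because irinotecan adds something, or because cetuximab by itself works in G13D. The second is the trial's own hypothesis for that cohort. A reader who takes 10% and 35% as monotherapy and combination rates, and the 80% as the power to separate them, would credit irinotecan with an effect that the powered test cannot isolate.

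**Working it through.** **1. The plan's own rates.** With exponential PFS, S(6) = 0.5^(6/median).

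- 1.8 months: 0.5^(6/1.8) = 9.9%, matching the stated 10%.
- 4.0 months: 0.5^(6/4.0) = 35.4%, matching the stated 35%.

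So the 10% and 35% come from these two medians. By the labels in Table 1 they are a no-cetuximab rate and an any-cetuximab rate.

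**2. The plan's own power.** Inputs: p0 = 15%, p1 = 40%, n = 25, α = 0.05, power 80%. An exact binomial search over one-sided two-stage designs gives the Simon optimal design: 7 patients in stage one, stop at 0 or 1 success, 25 in total, claim activity at 7 or more. Its α is 0.049 and its power 0.806. The stated figure is therefore reproduced as a one-arm test against a fixed 15%.

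**3. The same rates as a randomised comparison.** Normal approximation: z = [(p2 − p1) − z_α·√(2p̄(1−p̄)/n)] / √{[p1(1−p1) + p2(1−p2)]/n}, with n = 25 per arm.

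- 15% v 40%, two-sided: (0.25 − 1.96 × 0.1263)/0.1212 = 0.02, power 51%. One-sided: (0.25 − 1.645 × 0.1263)/0.1212 = 0.35, power 64%.
- 30% v 55%, two-sided: (0.25 − 1.96 × 0.1398)/0.1353 = −0.18, power 43%. The 30% is Table 1's wild-type cell ("6 m PFS cetuximab = 30" per cent).

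**4. Chance that Arm B beats 15% when irinotecan adds nothing.** Arm B then has the monotherapy rate. The article gives no final cut-off, so three rules are shown. The first is the optimal design from step 2; the other two use the article's futility rule (stop only at 0 of 7).

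| True six-month PFS | Stop ≤1/7, pass ≥7/25 | Stop 0/7, pass ≥8/25 | Stop 0/7, pass ≥7/25 |
|---|---|---|---|
| 8% (cetuximab alone, KRAS unknown) | 0.002 | 0.001 | 0.003 |
| 11.2% (1.9 months, cetuximab-treated KRAS mutant) | 0.012 | 0.004 | 0.016 |
| 15% (null) | 0.049 | 0.025 | 0.066 |
| 35% (cetuximab-treated G13D) | 0.685 | 0.681 | 0.805 |

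The pass probability is 68–80% at 35%, and below 2% at 8–11%.

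**The case against.** **Table 1 also supports a low monotherapy rate.** It gives 8% for cetuximab alone in the BOND study, under 5% at six months in KRAS mutants, and 1.9 months (about 11%) in cetuximab-treated KRAS mutants. BOND's 8% v 30% is the only alone-versus-combination row and lies close to 10% v 35%. This stands: if G13D behaves like other KRAS mutants on cetuximab alone, 15% is a cautious benchmark. But BOND's patients were not selected by KRAS status, and BOND is not the source cited for 1.8 and 4.0. A reader might infer that Table 1 puts all cetuximab-treated patients at 30–37%. It does not; that range covers only the wild-type and G13D columns.

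**The origin of 1.8 is inferred.** It is matched to a cell in Table 1, and reference 11 itself is not at hand. It may report monotherapy separately. What is established is that text and table conflict.

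**The trial has a concurrent randomised arm.** Allocation is 1:1 and PFS effects are described by Cox hazard ratios, so irinotecan's contribution can be estimated. The futility section already frames the Simon design as a test of the combination's activity. The article never says that beating 15% would prove an irinotecan effect. All this stands and limits the defect to the labels and to what the 80% refers to.

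**A time-to-event comparison is more efficient.** Under proportional hazards, 15% v 40% implies HR = ln 0.40/ln 0.15 = 0.483. Power is Φ(√d/2 × 0.728 − z_α): for d = 45 to 50 events, about 69–73% two-sided and 79–82% one-sided. That is a different calculation from the one the article describes, and it rests on nearly every patient having an event. It is a reason to state the comparative power, not to borrow the Simon figure.

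**Wild type.** A reader might apply the 15% benchmark to the wild-type cohort, where Table 1 shows 30% on cetuximab. The documents do not support this: 15% to 40% is stated for the G13D component, the Simon design is applied to that group only, and only the size of effect is tied to wild type.

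**Conclusion.** The point holds as a contradiction within one section, with a consequence for interpretation. The medians called monotherapy and combination are, as tabulated, no-cetuximab and any-cetuximab figures. The stated 80% power is that of a one-arm Simon test of Arm B in G13D against a fixed 15%; on six-month rates the randomised comparison has about 51% power two-sided or 64% one-sided.

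How far passing that test could mislead about irinotecan depends on an unknown, the monotherapy rate in G13D: 68–80% passes with no irinotecan effect at 35%, under 2% at 8–11%. These figures rest on exponential PFS for the 35% and 11%, on reconstructed final cut-offs, and on 4.0 months being an any-cetuximab figure. It would be tempting to treat 35% as the expected Arm A rate in G13D. Table 1 gives no pure monotherapy rate there, so it can serve only as the upper end of a range.

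**What to change.** 1. Reconcile the text with Table 1: relabel 1.8 months (10%) as the no-cetuximab benchmark and 4.0 months (35%) as any cetuximab, or cite the actual source of a monotherapy median.
2. State that the Simon test and its 80% power address only the activity of the combination in G13D against a fixed 15%.
3. State that conclusions about irinotecan come only from the randomised comparison of Arms A and B, and give its power: on six-month rates at 25 per arm, about 51% two-sided (64% one-sided) for 15% v 40%, and about 43% two-sided for 30% v 55%. If a time-to-event test is intended, give its power with the assumed number of events and the sidedness.
4. Show the Arm A rate in G13D as an assumed range, about 8% to 35%.

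The cost is wording and a restated power calculation. The claim attached to a positive Simon result becomes narrower; no patients are added and the design is unchanged.
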